### Sample size estimation

Previous studies have shown that the effect size for pain is 0.38–0.49 [52, 53]. The sample size was estimated by using G-Power software (version 3.1.9.6, Heinrich-Heine-Universität Düsseldorf, Düsseldorf, Germany) with the following parameters: analysis of variance (ANOVA) with repeated measures, a type I error of 5% (*α* = 0.05), a power of 95% (*β* = 0.05), group numbers = 4, number of measurements = 3, and effect size = 0.38. The total sample size of this study should be a minimum of 84 participants. With a possible dropout rate of 15%, it is estimated that a sample size of 25 patients per group will be needed to verify our study hypotheses for the primary outcomes.

### Statistical analyses

All data will be expressed as mean ± standard deviation (SD). A linear mixed model with repeated measures will be run to assess the data for fixed factors of the trial (LL group, High BFR group, Low BFR group, and HE group) and time (primary and secondary outcomes). Additionally, two-way ANOVAs will be used to analyze the differences between baseline, post-intervention, and follow-up measurements. Data from all subjects will be included in the statistical analyses, and the ITT approach will be applied to avoid disrupting the randomization of groups from dropping out through the trial. Any subject who started treatment will be included in the final outcome analysis regardless of whether he/she completed the study. Additionally, the missing data will be multiply imputed using chained equations with predictive mean matching, imputing data for each group separately. Estimates from 10 imputed data sets were combined using Rubin’s rules [54]. The level of significance will be set at *P* < 0.05 for all data. Statistical analyses will be performed using SPSS 22.0 (SPSS Inc., Chicago, USA).

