### Outcome measures

#### Primary outcome measure

Pain

A VAS will be used to evaluate pain intensity at rest and under maximum situations during the last week. The VAS comprises a line with a length of 100 mm, in which “0 mm” corresponds to no pain and “100 mm” to the worst pain imaginable [40]. The VAS depicts pain effectively and is easily operated and widely applied in patients with KOA. The VAS will be evaluated at baseline and 12 and 24 weeks after the randomization of the participants. Notably, the minimal clinically important improvement for pain is about 20 mm/100 mm [41].

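### The mixed model lists only group and time, two-way ANOVAs cover the same visits, and neither is named as decisive, so the primary treatment effect may be read from a group term diluted by baseline

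*Protocol article*

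**What the plan says.** All places are in the protocol article.

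- **Statistical analyses**, model terms: "A linear mixed model with repeated measures will be run to assess the data for fixed factors of the trial". The list of factors reads: "fixed factors of the trial (LL group, High BFR group, Low BFR group, and HE group) and time (primary and secondary outcomes". No interaction, baseline covariate or visit-specific contrast is mentioned.
- **Statistical analyses**, second method: "Additionally, two-way ANOVAs will be used to analyze the differences between baseline, post-intervention, and follow-up measurements". One 5% significance level applies throughout, and no order of priority is set between the two methods.
- **Primary outcome measure**: "The VAS will be evaluated at baseline and 12 and 24 weeks after the randomization of the participants". One of the three VAS assessments therefore precedes treatment.
- **Secondary outcome measures**: WOMAC follows the same three visits. TUG, muscle strength, muscle thickness and SF-36 are measured at baseline and 12 weeks only.
- **Sample size estimation**: a repeated-measures ANOVA with 5% type I error, 95% power and "group numbers = 4, number of measurements = 3, and effect size = 0.38", leading to: "The total sample size of this study should be a minimum of 84 participants". After 15% dropout this becomes 25 per group.
- **Discussion**: effects at 12 weeks and, for pain and self-reported function, at 24 weeks are to be examined as separate questions.

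**The concern.** Randomisation makes the expected difference between arms zero at baseline. If baseline is one of the repeated responses and the model has group and time effects without their interaction, the group coefficient averages the post-treatment effect with that zero. It then understates the effect and cannot give separate effects at weeks 12 and 24, although the Discussion promises both.

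The second issue stands whichever model is meant. Two analyses of the same primary data are planned at the same significance level, and nothing says which one, which contrast or which visit decides. If they disagree, the choice would be made after the results are known.

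**Working it through.** **Inputs from the article.** k = 4 groups, m = 3 measurements, f = 0.38, alpha = 0.05, target power 0.95, minimum N = 84, planned N = 100, and a clinically important improvement of about 20 mm on the VAS. **Assumption.** The within-patient correlation rho is not stated. I use 0.5, with a range of 0.3 to 0.7.

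**1. Reproducing N = 84.** For the between-factors (group main effect) test, lambda = f² × N × m / (1 + (m − 1) × rho) with df (k − 1, N − k).
- At rho = 0.5: lambda = 0.1444 × 84 × 3 / 2 = 18.19, df (3, 80), power 0.952. At N = 80 power is 0.941, so 84 is the smallest multiple of four that reaches 95%.
- At the same rho, the within-between interaction option would have given N = 28 and the within-factors option N = 20.
- Dropout: 84 / 0.85 = 98.8, rounded up to 99, which agrees with 25 per group.

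The stated figure therefore matches a test of group averaged over three measurements, one of which is baseline.

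**2. Dilution.** With effects 0, d, d at baseline, week 12 and week 24, the group coefficient of a group-plus-time model is (0 + d + d) / 3 = 2d/3.
- VAS: 20 mm × 2/3 = 13.3 mm. A small simulation (two arms of 25, true effect 20 mm at both later visits) gave about 13 mm for this coefficient. Adding group-by-time recovered about 19 mm.
- Outcomes at baseline and week 12 only: (0 + d) / 2 = d/2.

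**3. Power with f = 0.38 at both post-treatment visits and 0 at baseline.**
- Group main effect: effective f = 0.38 × 2/3 = 0.253. At rho = 0.5 and N = 84, lambda = 18.19 × 4/9 = 8.09.
- Group-by-time interaction: lambda = N × f² × (2/3) / (1 − rho), df (6, 2(N − 4)). At rho = 0.5 and N = 84, lambda = 16.17.
- Baseline-adjusted week 12: lambda = N × f² / (1 − rho²), df (3, N − 5). At rho = 0.5 and N = 84, lambda = 16.17.

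| Test | N | rho 0.3 | rho 0.5 | rho 0.7 |
|---|---|---|---|---|
| Group main effect, baseline included | 84 | 74% | 64% | 55% |
| Group main effect, baseline included | 100 | 82% | 72% | 64% |
| Group-by-time interaction | 84 | 70% | 86% | 98% |
| Group-by-time interaction | 100 | 79% | 92% | >99% |
| Baseline-adjusted, week 12 | 84 | 86% | 92% | 99% |
| Baseline-adjusted, week 12 | 100 | 92% | 96% | >99% |

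**4. Information relative to the baseline-adjusted week-12 comparison.** The ratio is (2/3)² / ((1 + 2 × rho) / 3) × (1 − rho²). At rho = 0.5 this is 0.444 / 0.667 × 0.75 = 0.50. It is 0.76 at rho = 0.3 and 0.28 at rho = 0.7.

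**The case against.** The strongest reply is that the article gives no model formula. Naming two factors is common shorthand for a factorial model, and the Discussion's separate 12-week and 24-week effects require group-by-time terms. Nor does the article say outright that baseline is a response in the mixed model. Baseline as a response is legitimate once the interaction is included, and covariates and covariance structure are details that an article may leave to a fuller document. These points stand, and they make the dilution conditional. They do not settle which analysis decides, and the match of N = 84 to a main-effect test points away from the factorial reading.

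The power figures are also open to challenge. They depend on an unstated correlation, and they place f = 0.38 at the post-treatment visits. If f = 0.38 is itself the effect averaged over all three measurements, the planned 95% holds. That is correct, but with no difference expected at baseline it requires post-treatment effects averaging 1.5 times as large (f = 0.57).

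Stronger readings that a reader might infer are not supported:
- **That the primary estimate is certainly biased toward zero.** This needs both an omitted interaction and a group main effect taken as the treatment effect, and the article states neither.
- **That the ANOVAs ignore within-patient correlation and so inflate the type I error.** Sample size estimation specifies a repeated-measures ANOVA, and nothing says the later ones are ordinary two-way analyses.
- **That the 13.3 mm figure carries over to WOMAC.** The two-thirds factor would apply, but WOMAC is a score out of 120, not millimetres.

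**Conclusion.** The point holds as an ambiguity in the primary analysis with a potentially large consequence. It is not a demonstrated bias. What is certain is that two methods at the same significance level cover the same primary data and neither is named as decisive. That the diluted group main effect is the intended test is probable, because N = 84 reproduces under it, but that match itself rests on the assumed correlation of 0.5.

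If that effect is taken as the treatment effect, the VAS result shrinks to two thirds when the benefit is sustained, outcomes with two visits shrink to one half, and the two time points cannot be separated. At the planned N = 100, power would be 72% (82% to 64% over correlations 0.3 to 0.7). A properly tested interaction would avoid the dilution, with 92% at correlation 0.5, and a baseline-adjusted week-12 comparison would have 96%. All these are four-arm omnibus tests that assume f = 0.38 at each post-treatment visit they use.

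**What to change.** Name one primary analysis in Statistical analyses: a linear mixed model on week-12 and week-24 VAS, with baseline VAS as covariate and group, time and group-by-time as fixed effects. Take the between-arm contrasts at one named visit, for example week 12, as the primary estimate. Use baseline-adjusted ANCOVA for TUG, muscle strength, muscle thickness and SF-36. Drop the two-way ANOVAs, or label them supportive and state that they do not decide the primary outcome.

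The cost is rewording one paragraph. Every measurement needed is already planned, and since the article reports recruitment as still in progress, the change can be made before the outcome data are analysed.

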**Methods:**

This is a study protocol for a randomized, controlled trial with blinded participants. One hundred individuals will be indiscriminately assigned into the following groups: two training groups with a BFR at 40% and 80% limb occlusion pressure (LOP), a training group without BFR, and a health education group. The three intervention groups will perform strength training for the quadriceps muscles twice a week for 12 weeks, while the health education group will attend sessions once a week for 12 weeks. The primary outcome is pain. The secondary outcomes include self-reported function, physical function performance, muscle strength of the knee extensors, muscle mass of the quadriceps, quality of life, and adverse events. Intention-to-treat analysis will be conducted for individuals who withdraw during the trial.

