### Randomization and allocation concealment

Eligible patients will be randomly assigned to one of the following groups at a ratio of 1:1:1:1: LL group, High BFR (80% LOP) group, Low BFR (40% LOP) group, and HE group. The research staff will independently use SAS software (SAS Institute, Cary, NC, USA) to generate a randomization sequence; this staff will not participate in the intervention or statistical analyses in the study. The number sequence will then be placed into a sequentially numbered, sealed, opaque envelope prior to the study by another independent research assistant who will also not participate in other parts of this study. Once the eligible patients with KOA complete the informed consent process, their demographic information and baseline measures will be recorded. Next, the research coordinator, who will not be involved in the measurement process, will have the authorization to open the envelopes in ascending order to determine a patient’s intervention group assignment.

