### Masking

The participants will be informed that all of the interventions have proven efficiencies for their knee disorders, but it is still unknown which intervention works best. Moreover, they will be asked not to discuss their intervention content and group assignment at any time during the study. The intervention locations and times of intervention sessions will be separated for each individual. Unmasking will only be allowed in the case of severe adverse events and will be reported as part of the results of this study.

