## Discussion

BFR training has become a novel intervention for lower limb degeneration or post-surgical musculoskeletal disorders. However, there have been no consistent recommendations for BFR training in treating KOA in any guidelines until now. In this trial, we will investigate the efficacy of LLRT combined with different BFR pressures (0%, 40%, and 80% LOP) on pain, self-reported function, physical functional performance, muscle strength, muscle mass, and QoL.

Although several studies have indicated that BFR combined with LLRT is more effective than LLRT alone [19, 20], the most efficacious degree of BFR has not been determined. If a 40% LOP during BFR will produce similar clinical outcomes as an 80% LOP during BFR in patients with KOA, resistance using a lower LOP can be a good choice for those who are unbearable for high degree of LOP. Additionally, there has been no study comparing the effects of BFR training with a control group without an exercise intervention, and a complete placebo control is not applicable for patients with KOA. Thus, we will set up a control group (the health education group), which will make the study more rigorous and objective. We believe our study will provide evidence for the effectiveness of RT with BFR, which is important for clinicians in treating patients with KOA.

This trial meets the requirements of methodology for the application of randomization, allocation concealment, and ITT approach, as well as masking for patients. In this trial, there will be two sessions per week for 12 weeks, yielding a total of 24 exercise sessions for the exercise intervention groups. We will investigate the short-term effects (12 weeks) of these four groups for all clinical outcomes and safety, as well as the mid-term (24 weeks) effects of pain and self-reported function.

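### The statistical section promises intention-to-treat for all subjects, then makes starting treatment the condition for analysis, so randomised patients who never start could be dropped under an ITT label

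*Protocol article*

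**What the plan says.** Two consecutive sentences in Statistical analyses describe who is analysed:

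- "Data from all subjects will be included in the statistical analyses, and the ITT approach will be applied to avoid disrupting the randomization of groups" (the sentence goes on to refer to dropout).
- "Any subject who started treatment will be included in the final outcome analysis regardless of whether he/she completed the study".

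The Discussion then states: "This trial meets the requirements of methodology for the application of randomization, allocation concealment, and ITT approach, as well as masking for patients".

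The order of events comes from Randomization and allocation concealment. First, "Once the eligible patients with KOA complete the informed consent process, their demographic information and baseline measures will be recorded". After that, the research coordinator "will have the authorization to open the envelopes in ascending order to determine a patient’s intervention group assignment". Baseline therefore precedes allocation, and allocation precedes the first session.

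Statistical analyses also plans a linear mixed model with repeated measures, and multiple imputation by chained equations carried out separately in each group.

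**The concern.** ITT means that everyone randomised is analysed in the arm assigned. The first sentence points that way without using the word randomised. The second sentence is the only one that states a condition, and the condition is starting treatment. An analyst could follow it, remove patients who were randomised but never attended, and still report the result as ITT.

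The gap matters because removal after allocation is no longer protected by randomisation. Three exercise arms attend twice-weekly machine-based sessions with a cuff on the thigh, which in the LL arm is a sham. The fourth arm attends a weekly education session. A patient who hoped for exercise can tell that health education is something else, so not starting could be more common there, or could involve a different kind of patient. Health education is the comparator for all three exercise arms in the first hypothesis, so a distortion in that one arm would enter three contrasts.

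**Working it through.** **1. The plan's own numbers.** Sample size estimation gives f = 0.38, 4 groups, 3 measurements, α = 0.05 and power 0.95, for a minimum of 84. The correlation between measurements is not stated. With ρ = 0.5 (assumed), the between-groups test has λ = f²·N·m/(1+(m−1)ρ) = 0.1444 × 84 × 3/2 = 18.19 on 3 and 80 degrees of freedom, and power 0.952. So 84 reproduces. Inflation for 15% dropout: 84/0.85 = 98.8, so 99, rounded up to 100 for four arms of 25. The point does not depend on this calculation; only the 25 per arm is used below.

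**2. The two readings side by side.**

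| Reading | Who is analysed | Number |
|---|---|---|
| All subjects, ITT | everyone randomised | 100 |
| Started treatment | those with a first session | 100 minus never-starters |

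The readings agree only if nobody is lost between envelope opening and first session. The document gives no never-starter rate, and its 15% dropout is not split by timing or by arm.

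**3. What dropping never-starters would do to an arm mean.** Let s of 25 patients never start, let those who stay have mean follow-up pain M, and let the never-starters have mean M + d. Then:

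- mean of all 25 = [(25−s)·M + s·(M+d)]/25 = M + (s/25)·d
- mean of starters only = M
- size of the shift = (s/25)·d

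Both s and d are assumptions. The top value, s = 4 (16%), corresponds to roughly the whole dropout allowance (0.15 × 25 = 3.75) falling before the first session.

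| s | d = 10 mm | d = 15 mm | d = 20 mm |
|---|---|---|---|
| 1 | 0.4 | 0.6 | 0.8 |
| 2 | 0.8 | 1.2 | 1.6 |
| 3 | 1.2 | 1.8 | 2.4 |
| 4 | 1.6 | 2.4 | 3.2 |

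Against the 20 mm important improvement in Primary outcome measure, this is 0.4/20 = 2% to 3.2/20 = 16%.

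**4. Direction.** If never-starters in health education have more pain than those who stay, dropping them lowers that arm's mean and works against the first hypothesis. If they have less pain, dropping them raises the mean and favours exercise. The document does not indicate which is more likely.

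**5. Effect on one comparison.** Take one exercise arm of 25 against health education, no true difference, one visit, no baseline adjustment and an assumed SD of 20 to 25 mm. The standard error is SD·√(1/25 + 1/(25−s)). At the unfavourable end (SD 20, s = 4, d = 20) it is 20·√(1/25 + 1/21) = 5.92 mm. A shift of 3.2 mm then raises the two-sided 5% error to about 8.4%. At the favourable end (SD 25, s = 1, d = 10) it stays at about 5.0%.

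**The case against.** A reader might infer that the analysis set is defined as treatment starters and that never-starters will be removed. The text does not say so. The started-treatment sentence is inclusive: it keeps starters who do not complete. It follows a sentence that promises data from all subjects for the sake of the randomisation. This objection stands, and the defect is therefore an inconsistency that permits exclusion, not an exclusion rule.

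A reader might also infer that patients will leave on learning their arm and so bias the comparison with health education. That too goes beyond the document. The coordinator opens the envelope, but the article does not say when the patient learns the assignment. The Participants section keeps out people who are unsure of staying for 6 months. The Masking section has patients told that every intervention is of proven benefit and that the best one is unknown. Both plausibly reduce early losses, though neither removes them or hides the difference between education and exercise.

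The millimetre figures rest on assumptions. If never-starters differ at baseline as well as at follow-up, a baseline-adjusted or change contrast would move by less than the table shows.

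The abstract's line, "Intention-to-treat analysis will be conducted for individuals who withdraw during the trial", is loosely worded, but it does not conflict with keeping withdrawals in the analysis and is not a separate error.

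**Conclusion.** The point holds as an inconsistency in Statistical analyses. All subjects are promised under ITT, the only stated condition is having started treatment, and the Discussion claims ITT without qualification. What is left open is whether a patient randomised but not started is analysed. Because the document states the rule and states it inconsistently, this is more than detail left to an analysis plan.

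Bias is possible, and it could depend on the arm, but neither its size nor its sign can be derived from the document. The 0.4 to 3.2 mm shift and the error rate of about 5.0% to 8.4% rest on the assumed number of never-starters, pain difference and SD. They indicate a modest effect, and none at all if every randomised patient starts.

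**What to change.** Replace the started-treatment sentence with: *All randomised participants, analysed in the allocated arm whether or not treatment was started.* The Discussion's ITT claim is then supported.

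No new patients or methods are needed. Never-starters have a baseline VAS, because baseline precedes envelope opening, and they enter through the planned mixed model or multiple imputation. The limit should be acknowledged: imputation within each group predicts their follow-up from patients in that arm who were observed, so it corrects only for selection that the observed data explain. Primary outcome measure counts its VAS visits from randomisation, so follow-up values obtained from never-starters willing to give them would reduce reliance on that assumption.

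The cost is one sentence, plus the notice of protocol changes to participants, ethics committee and registry that the data management section already requires. Trial status reports recruitment still in progress, so the wording could be settled before the final analysis.

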### Data management, monitoring, and quality control

The data will be carefully recorded by both printed and electronic case report forms (eCRFs). Only outcome assessors have access to the eCRFs, and all input data will be double-checked by two independent assessors. All data will be unmodifiable once input and checked through the eCRF. An independent Data and Safety Monitoring Board will be established from independent experts in orthopedics, physiotherapy, methodology, and statistics to review and interpret the trial data. The board will review the progress of the trial after 6 weeks and decide if premature closure of the study is required based solely on adverse events. The Institute of Sports and Health of China will be responsible for verifying the accuracy of the data. Only the statisticians will have access to the database to conduct final statistical analyses. The data collected from this trial will not be used in secondary or ancillary studies. In this trial, both online and on-site monitoring will be adopted to review the trial processes. The ethics committee of Beijing Sport University will monitor protocol violations weekly. The participants, ethics committee, and Chinese Clinical Trial Registry will be informed of any protocol modifications by email.

